## Research Period

Registration Period: From the date of permission (or the date of publication of the RCT) to February 28, 2023

Study Period: From the date of permission (or the date of publication ofthe J RCT) to May 31, 2023

Duration of participation: 6 months

## data collection

## Forms and Submission Deadlines

In this study, the results of the questionnaire before and after the intervention and the following items using Google Forms will be submitted to the principal investigator. The deadline for submission of the following items using Google Forms is within one week after the end of the patient's observation period.

## How to fill out

In the Google Form, the name of the pharmacy, the study registry number, the date of the intervention, the method of managing the medication at home (self-management, family management, facility management, caregiver management), the most recent meal at home (self-catering, home delivery meals, eating out), whether or not you want detailed nutritional guidance from a dietitian, the descriptive form for resting blood pressure at the time of visit, and the descriptive form for resting blood pressure at the time of visit.

The study registry number will be communicated from the principal investigator to the representative of each site after the patient consents to participate in this study. The study registry number, patient ID, and patient name will be prepared and kept by the principal investigator.

## How to send

For items in Google Forms, use the submission form on the Web. The results of the questionnaire will be sent by fax.

## Methods of statistical analysis

### Population to be analyzed

The main analysis of the primary endpoint and secondary endpoint is the one targeting the Full Analysis Set. In addition, we will also conduct an analysis of the Per Protocol Set to confirm the stability of the analysis results.

(1) Definition of Full Analysis Set

Cases that meet all of the following criteria are considered to be cases.

(1) eGFR less than 45 ml/min/1.73 m2 and serum potassium level of 4.0 mmol/L or more

(2) Patients who have obtained consent for this study at an insurance pharmacy

(2) Definition of Per Protocol Set

　　Patients with FAS who meet all of the following criteria are considered to be FAS.

(1) Patients who obtained the results of questionnaire 2 after 84 days after obtaining consent

(2) Patients with resting blood pressure after visiting the clinic after 84 days after obtaining consent

(3) Patients who responded to a questionnaire about their awareness of potassium restriction after the intervention

### Statistical analysis

(1) Primary endpoint

The mean and standard deviation of serum potassium levels before and after the intervention will be calculated, and a paired student's t-test will be performed at 5% on both sides of the significance level.

(2) Secondary endpoint

The mean and standard deviation of resting blood pressure before and after the intervention will be calculated, and a student's t-test will be performed with a significance level of 5% on both sides. For the content of the questionnaire, Fisher's exact test or chi-square test will be performed at a significance level of 5% on both sides of the change in awareness of potassium limitation.

(3) Comparison of patient backgrounds

Nutritional guidance will be used to compare the patient's background between the improved and non-improving serum potassium groups. For the nominal variables of gender, medical history, medication administration at home, and eating at home, Fisher's exact test or chi-square test is performed at 5% on both sides of the significance level. For the continuous variables age, Body mass index, and eGFR, the mean and standard deviation are calculated, and a student's t-test is performed with a correspondence of 5% on both sides of the significance level.

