## Summary of study design

Prospective intervention, before-and-after comparison, open design

This research will be conducted in compliance with the Personal Information Protection Law, the Declaration of Helsinki, and the Ethical Guidelines for Life Science and Medical Research Involving Human Subjects.

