### Secondary Objectives

| Secondary Objectives | Evaluation items | Reasons and Validity for Selection of Evaluation Items |
| --- | --- | --- |
| Change in Attitudes Toward the Intake of Potassium-Containing Foods | Survey Results | Evaluated on a 5-point scale for questions about awareness of potassium restriction |
| Change in resting blood pressure before and after intervention | Systolic and diastolic blood pressure at rest at visit | Blood pressure fluctuations are expected due to diet |

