## Observation items and methods

### Observations and information and samples to be collected

The blood and urine test data used in this study will not be newly tested because the data obtained in daily practice will be obtained retrospectively (retrospectively) through electronic medical records.

(Pre-intervention)

- Patient background: age, gender, body mass index, medical history (heart failure, diabetes), how to manage medications at home (family management or self-management), meals at home (self-catering, home delivery, eating out)
- Blood tests: serum albumin level, Na, Cl, K, Mg, aspartate aminotransferase, alanine aminotransferase, eGFR, blood urea nitrogen, red blood cell count, white blood cell count, Hemoglobin level, hematocrit, platelet count
- Urinalysis: urine albumin, urine albumin/creatinine ratio, or urine protein, urine protein/creatinine ratio
- Oral medications: presence or absence of concomitant medications (mineralocorticoid receptor antagonists, renin-angiotensin-aldosterone inhibitors, sodium glucose cotransporter2 inhibitors) that increase serum potassium levels, presence or absence of concomitant medications (loop diuretics) that reduce serum potassium levels, presence or absence of potassium adsorbents
- Vitals: Resting blood pressure (systolic and diastolic) after visiting the station

In addition, if the blood pressure at home is recorded in the blood pressure notebook, it is possible to substitute the resting blood pressure after the visit.

(12 weeks after intervention)

- Patient background: age, gender, body mass index, medical history (heart failure, diabetes), how to manage medications at home (family management or self-management), meals at home (self-catering, home delivery, eating out)
- Blood tests: serum albumin level, Na, Cl, K, Mg, aspartate aminotransferase, alanine aminotransferase, eGFR, blood urea nitrogen, red blood cell count, white blood cell count, Hemoglobin level, hematocrit, platelet count
- Urinalysis: urine albumin, urine albumin/creatinine ratio, urine protein, urine protein/creatinine ratio
- Oral medications: presence or absence of concomitant medications (mineralocorticoid receptor antagonists, renin-angiotensin-aldosterone inhibitors, sodium glucose cotransporter2 inhibitors) that increase serum potassium levels, presence or absence of concomitant medications (loop diuretics) that reduce serum potassium levels, presence or absence of potassium adsorbents

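### The t-test labels for blood pressure and for the background comparison look swapped, and no rule keeps a patient's two blood-pressure readings to one source

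*Protocol*

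**What the plan says.** Protocol section 3.5.2 contains three t-tests.

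- Serum potassium (primary): "a paired student's t-test will be performed at 5% on both sides of the significance level".
- Blood pressure (secondary): the mean and SD of "resting blood pressure before and after the intervention will be calculated, and a student's t-test will be performed with a significance level of 5" per cent, two-sided. Neither paired nor unpaired is stated.
- Patient backgrounds: the aim is to "compare the patient's background between the improved and non-improving serum potassium groups". For age, BMI and eGFR, "a student's t-test is performed with a correspondence of 5% on both sides of the significance level".

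Section 0.1 gives the design as "Prospective intervention, before-and-after comparison, open design". It is a single group with no control.

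Section 2.1.2 defines the blood-pressure endpoint as "Systolic and diastolic blood pressure at rest at visit". In section 3.6.1, the pre-intervention list and the 12-week list each add the same permission: "if the blood pressure at home is recorded in the blood pressure notebook, it is possible to substitute the resting blood pressure after the visit". Nothing says that one patient's two readings must come from the same place. The description of the Google Form in section 3.4 mentions resting pressure at the visit but no field for where a reading was taken.

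**The concern.** Blood pressure has the same data structure as potassium: one value before and one after in each patient. Potassium is explicitly paired and blood pressure is not. The only other t-test, between two groups of different people, carries the wording that suggests pairing. The simplest explanation is that the two labels changed places.

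An analyst who followed the text literally would run a two-sample test on paired blood-pressure data and discard the within-patient correlation. The same analyst would then find no pairs on which to run the background test. Section 3.5.3 repeats the section 3.5.2 analyses in each subpopulation, so the wording carries over to smaller samples.

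The source of the reading is a separate matter. If a patient is measured in the pharmacy at one time and represented by a home value at the other, the change includes the difference between settings. No control arm is available to remove it.

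**Working it through.** **1. The three tests side by side**

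| Comparison | Same patients on both sides? | Test that fits | Wording in section 3.5.2 |
|---|---|---|---|
| Potassium, before/after | Yes | Paired | Paired |
| Blood pressure, before/after | Yes | Paired | Pairing not stated |
| Age, BMI, eGFR, improved vs non-improving | No | Independent samples | Reads as paired |

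In the third row, nothing links an improved patient to a particular non-improving one, and the group sizes are set by the outcome. If 40 patients split 25 and 15 (an illustration), no paired statistic exists.

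**2. The plan's own figure**

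Section 3.2.2 gives n = 34 for a paired t-test with difference 0.5 and SD 1.0 mmol/L. I take two-sided α = 0.05 and power 0.80; the printed α and β labels are a separate matter. From the noncentral t with noncentrality 0.5√n, power is 0.795 at n = 33 and 0.808 at n = 34. The figure reproduces and depends only on the potassium test. The protocol gives no sample-size figure for blood pressure.

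**3. Two-sample test applied to before/after blood pressure**

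Assumed inputs, none of them in the protocol: SD s = 18 mmHg at each time, true fall 6 mmHg, correlation r from 0.4 to 0.8. From the protocol: n = 40.

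- Standard error of the mean change, paired: s√(2(1−r)/n).
- Standard error used by the two-sample test: s√(2/n) = 18 × √(2/40) = 4.02 mmHg.
- Ratio: 1/√(1−r).

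At r = 0.6 the paired standard error is 4.02 × √0.4 = 2.55 mmHg, so the two-sample value is 1/√0.4 = 1.58 times too large. Paired power comes from the noncentral t. Two-sample power and type I error come from simulation (200,000 simulated trials per setting).

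| r | Paired SE (mmHg) | SE ratio | Power, paired | Power, two-sample | Actual type I error, two-sample |
|---|---|---|---|---|---|
| 0.4 | 3.12 | 1.29 | 47% | 27% | 1.2% |
| 0.6 | 2.55 | 1.58 | 63% | 23% | 0.2% |
| 0.8 | 1.80 | 2.24 | 90% | 16% | below 0.01% |

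A second check avoids assuming an SD or a fall. Set the effect so that the paired test has 80% power at n = 34, and vary r. The two-sample test then has power of about 81% at r = 0, 69% at 0.3, 53% at 0.5 and 25% at 0.7 (40,000 simulated trials each). The loss depends on positive correlation and vanishes without it. Both tests use the same numerator, the mean after minus the mean before, so for patients with both readings the estimate is the same.

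**4. Mixed sources**

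Shift in mean change = (share going pharmacy to home − share going home to pharmacy) × (home − pharmacy difference). The shares and the setting difference are assumptions.

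| Net share switching | Difference 3 mmHg | 5 mmHg | 8 mmHg |
|---|---|---|---|
| 10% | 0.3 | 0.5 | 0.8 |
| 20% | 0.6 | 1.0 | 1.6 |
| 50% | 1.5 | 2.5 | 4.0 |

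At a net 20%, the shift of 0.6 to 1.6 mmHg is 10% to 27% of the assumed 6 mmHg fall (0.6/6 and 1.6/6). With equal switching in both directions the net share is zero and only noise is added.

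**The case against.** The best defence is that the text reads like a rough translation and that the intention can be guessed. A reader might infer that the protocol prescribes an unpaired test for blood pressure. It does not: that word does not appear in section 3.5.2, and a before-and-after comparison in a declared before-and-after design can be read as implicitly paired. The wording of the background test is also garbled, and its paired meaning is an interpretation. This lowers the claim from a wrong test to unclear labels that point the wrong way. It does not remove the need to correct them, because pairing is marked explicitly for potassium in the same section.

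A reader might also infer that home readings are allowed at one time point only. They are not; the permission stands in both lists of section 3.6.1. What is missing is a rule within the patient. Substitution is also optional: pharmacy measurement is scheduled at Day 1, at the visits between and from Day 84, and the Per Protocol Set asks for a post-visit resting pressure after 84 days. Whether a notebook value satisfies that criterion is not stated, and mixed pairs may be few.

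Two further points stand. The two-sample test is conservative, so it would not manufacture a blood-pressure finding. And the study describes itself as exploratory, with blood pressure as a secondary endpoint.

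**Conclusion.** The concern holds as a fault of specification. Blood pressure lacks the pairing stated for potassium, and the background comparison carries wording that reads as pairing and cannot be used there.

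If followed literally, the cost for blood pressure is lost power and intervals that are too wide: at assumed r = 0.6, a standard error 1.58 times too large and 23% power instead of 63%. It is not a biased estimate or an inflated false-positive rate.

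The source of readings is where bias could enter, and only through net switching: 0.6 to 1.6 mmHg under an assumed net 20% and a 3 to 8 mmHg difference. The protocol gives no basis for saying that such switching will happen or in which direction.

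Severity is minor to moderate. A reading in which the trial's main conclusion is at risk is not supported: the potassium test is correctly paired and n = 34 does not depend on any of this.

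**What to change.** 1. In section 3.5.2 (2), state a paired t-test for the change in systolic and in diastolic pressure, and report the mean change with its 95% confidence interval.
2. In section 3.5.2 (3), state an independent-samples t-test for age, BMI and eGFR between improved and non-improving patients.
3. In section 3.6.1 and on the Google Form, record the source of each reading (pharmacy or home notebook), and use the same source at both time points for each patient where available.
4. Keep the Full Analysis Set as the main analysis, as section 3.5.1 requires, and add a sensitivity analysis restricted to same-source pairs.

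The cost is a few words, one extra form field and one small analysis. The sensitivity analysis loses the mixed pairs: if 20% of patients were mixed, that is 0.20 × 40 = 8 patients, which is a reason not to make the restriction the main analysis.

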### Subpopulation analysis

A subpopulation of patients with serum potassium levels greater than or equal to 5.0 mmol/L or less than 5 mmol/L at the time of patient enrollment and low or high awareness of potassium restriction will be generated, and each subpopulation will be analyzed at 3.5.2.

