# Basis for the scientific rationality of the study

It has been reported that the amount of potassium excreted in the urine decreases in CKD stage G3b or later6^)^ and the risk of hyperkalemia is high7^).^ In recent years, it has been shown that pharmacists at community pharmacies improved patient outcomes by providing nutritional guidance for hypertension 8) and diabetes mellitus 9) for a few minutes, in addition to conventional medication guidance. Therefore, it is thought that providing nutritional guidance to CKD patients by pharmacy pharmacists may motivate them to follow a diet at home and contribute to the optimization of serum potassium levels.

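### The background comparison splits a continuous potassium change into improved and non-improving groups, which costs about 20–30 points of power and can mislead for variables that track the baseline reading

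*Protocol*

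**What the plan says.** Section 3.5.2 of the Protocol (Statistical analysis), item (3), sets out to compare patient backgrounds "between the improved and non-improving serum potassium groups".

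- **Categorical variables.** "For the nominal variables of gender, medical history, medication administration at home, and eating at home", it prescribes Fisher's exact or chi-square tests at 5% two-sided.
- **Continuous variables.** "For the continuous variables age, Body mass index, and eGFR, the mean and standard deviation are calculated", followed by a t-test: "a student's t-test is performed with a correspondence of 5% on both sides of the significance level".

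That makes seven listed variables, each tested alone. Baseline potassium is not among them, no adjustment is stated, and no cut-off defines improvement.

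Baseline potassium does appear in section 3.5.3 (Subpopulation analysis), which forms strata by "serum potassium levels greater than or equal to 5.0 mmol/L or less than 5 mmol/L at the time of patient enrollment" and states that "each subpopulation will be analyzed at 3.5.2". Item (3) is therefore also to be run within each stratum.

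**The concern.** Two things look wrong with the method, and defining improvement would cure neither.

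1. **Lost information.** A patient whose potassium falls by 0.05 mmol/L and one whose potassium falls by 0.8 count the same under any simple fall/no-fall rule, and any other cut-off has the same weakness. In a study this small the loss matters.
2. **Starting level.** A single high reading tends to be followed by a lower one, so belonging to the improved group partly reflects a high baseline reading. There is no control group to separate such chance falls from benefit. A background variable that moves with the baseline reading could then look like a predictor of response.

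At stake is what the study reports about which patients did well. The primary paired comparison is not affected.

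**Working it through.** **Sample size available.** The Protocol's rationale uses a mean difference of 0.5 and an SD of 1.0 mmol/L in a paired t-test. The exact two-sided calculation at 5% and 80% power gives n=34 (power 80.8%), so the stated figure reproduces. The normal approximation gives (1.960+0.842)² × (1.0/0.5)² = 31.4, so 32. The text prints the values of α and β the wrong way for this result; taken literally they give 12. The target of 40 corresponds to 34/0.85. The range for item (3) is thus n=34 to 40.

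**Inputs.** From the Protocol: between-person SD about 0.5 mmol/L, entry at potassium 4.0 mmol/L or more, n=34–40. Assumed, because the Protocol gives no value: mean potassium 4.6 or 4.7, pre/post correlation 0.5–0.7, mean fall 0–0.2, the effect of a modifier, and how a background variable relates to potassium. *Improved* is taken as follow-up below baseline.

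**Power (simulated, pre/post correlation 0.6, mean fall 0.2).**

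| n | Modifier effect per SD | Two-group test | Continuous models |
|---|---|---|---|
| 40 | 0.15–0.20 mmol/L | 33–54% | 54–84% |
| 34 | 0.15–0.20 mmol/L | 30–47% | 49–77% |

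At n=40 the gap is 54−33 = 21 points at the low end and 84−54 = 30 at the high end. A separate calculation that assumes only a correlation of 0.4 between the variable and the change gives 75% against 49–53% at n=40, and 66–67% against 44–46% at n=34. The loss does not depend on any argument about regression to the mean.

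**How far improvement reflects the starting level.** Write each reading as a stable level plus a fluctuation, with pre/post correlation ρ. Without the entry rule, the correlation of baseline with change is −√((1−ρ)/2). This is −0.50 at ρ=0.5 and −0.42 at ρ=0.64. With the entry rule, simulation gives −0.37 to −0.45. With no intervention effect (mean 4.7), 71–75% of patients at 5.0 or above improve, against 44–45% of those between 4.0 and 5.0. Within the two strata the correlation is still about −0.23 to −0.29.

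**When a listed variable becomes a false predictor.** Change equals the second fluctuation minus the first, so the stable level cancels. A variable related only to the stable level is uncorrelated with change, apart from a slight effect of the entry rule. A variable that tracks the baseline reading inherits its correlation with change: at ρ=0.5 and an assumed correlation of −0.5, that is (−0.5) × (−0.5) = 0.25.

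For that second kind of variable, irrelevant once baseline is known, the two-group test is significant in about 9–15% of trials, against about 5% for baseline-adjusted regression. The table shows how the answer turns on the kind of variable (n=40, no effect on change, stable and fluctuating SD 0.35 each, entry rule applied, 1,500 runs).

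| Variable correlates with | Two-group test | Change, no baseline | Follow-up, adjusted for baseline |
|---|---|---|---|
| Neither | 5% | 5% | 5% |
| Stable level, 0.4 | 5% | 5% | 17% |
| Stable level, 0.6 | 6% | 6% | 38% |
| Both parts, 0.3 each | 13% | 18% | 5% |
| Fluctuation only, 0.4 | 26% | 37% | 17% |

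Neither continuous model holds 5% in every row. Over the assumptions examined, adjustment gives about 16–37% for a variable tracking the stable level. The 38% here agrees within simulation error, since √(0.38×0.62/1500) is about 1.3 points.

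**The case against.** The strongest reply is that item (3) is a side table. It is not among the primary or secondary objectives, and the Protocol calls the study exploratory. A responder/non-responder table is a common descriptive device. This limits the importance of the point, but the item prescribes 5% tests, so it is more than description.

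Three stronger readings are tempting, and the documents do not support them.

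- **That any variable related to baseline potassium will look like a predictor.** Regression to the mean makes baseline potassium itself a spurious predictor, and item (3) does not test it. Age, sex, BMI, history, medication management and meals change slowly and would plausibly relate to the stable level, where the error rate stays near 5–7%. eGFR is the likeliest exception, because the Protocol lists it in the same routine blood panel as potassium. The rationale in section 5, "It has been reported that the amount of potassium excreted in the urine decreases in CKD stage G3b or later", does not settle this: every enrolled patient is already at that stage, and no correlation within the sample is given.
- **That the plan ignores baseline potassium.** Section 3.5.3 repeats the analyses on either side of 5.0 mmol/L. This reduces the problem without removing it, leaves very small groups, and keeps the full-sample comparison.
- **That adjusting for baseline is the cure.** For a variable that tracks the stable level, adjustment creates false predictors that the two-group test does not.

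**Conclusion.** The point holds as a moderate one: worth changing, without threat to the primary analysis. The firm part is the power loss of about 20–30 percentage points under assumed modifier effects of 0.15–0.20 mmol/L per SD. It appears in every power scenario examined and alone justifies the change.

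The false-predictor part is conditional. It applies to a variable that tracks the baseline reading (about 9–15% at an assumed correlation of −0.5) and not to one related only to the stable level. The Protocol gives no mean potassium, pre/post correlation, variance components or covariate correlations, so the figures show direction and rough size only.

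Seven separate 5% tests would, if independent, give at least one false positive with probability 1 − 0.95⁷ = 30%. That is a further reason to label the results exploratory.

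**What to change.** Replace the two-group tests in item (3) with linear regression that keeps potassium continuous, for each background variable X in turn, and report both models:

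- change: K(follow-up) − K(baseline) = a + b·X + error
- adjusted: K(follow-up) = a + b·X + c·K(baseline) + error

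Categorical variables enter as indicators. Give each b with its 95% CI and state that the analysis is exploratory. Where the two models disagree, say so and draw no conclusion about that variable. Agreement is reassuring but not proof, since a variable tracking only the fluctuation misleads both.

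Keep the improved/non-improving table as description without tests, and state how improvement is defined for it. This also removes the t-test whose wording reads as paired, which cannot apply to two separate groups of patients.

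The cost is a change of wording and a slightly less simple presentation. The variables are already collected at baseline and follow-up, and no extra patients or measurements are needed.
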